## Abstract

**Background:**

An Organised Cervical Cancer Screening Programme (OCCSP) was started in Poland in 2006/2007. Each woman aged 25 to 59 is eligible for a free Pap test every 3 years in OCCSP. Despite implementation of the OCCSP, the age-standardised cervical cancer (CC) incidence and mortality rates in 2019 were 7.3/100 000 and 3.9/100 000 respectively and were still higher than those in Western European countries with well-organised screening programmes. Apart from low coverage of the OCCSP, suboptimal performance of the screening test (conventional cytology) may be partially responsible for this situation. Several countries have already incorporated high risk Human Papillomavirus (hrHPV) testing in CC screening as a more sensitive tool reducing the risk of missing precancerous lesions and allowing for extension of screening intervals. The European Guidelines for Quality Assurance in Cervical Cancer Screening recommend pilot evaluation of a new screening test in country-specific conditions before its implementation.

**Methods:**

The HIPPO project (HPV testing In Polish POpulation-based cervical cancer screening program) is a randomised health services study nested in the OCCSP in Poland. The project will randomise 33 000 women aged 30–59 years to cytology or hrHPV testing (ratio: 1:1) with age stratification. In the cytology arm women with repeated Atypical Squamous Cells of Undetermined Significance (ASC-US) or ≥ Low–Grade Squamous Intraepithelial Lesions (LSIL) are referred for colposcopy. In the other arm, hrHPV ( +) women with ≥ ASC-US reflex Liquid-Based Cytology (LBC) are referred for colposcopy. Primary endpoints include detection rates of histologically confirmed high grade intraepithelial lesions or worse (CIN2 +) in each arm.

**Discussion:**

This pilot randomised healthcare study nested in the OCCSP in Poland will assess and compare the performance of hrHPV testing to current standard—cytology in order to make decisions on implementation of HPV-based screening in the country.

**Trial registration:**

This randomised healthcare service study was prospectively registered at https://clinicaltrials.gov/ (identifier: NCT04111835, protocol ID 28/2019) on 19th of September 2019.

## Background

In 2006/2007 an Organised Cervical Cancer Screening Programme (OCCSP) was implemented in Poland. It comprised personal invitations of women aged 25–59 years to have a screening Pap test every three years. By the decision of the Ministry of Health related to high costs, uncertain effectiveness and issues with access to personal data, the postage of personal invitations for cytology was stopped in 2016. Currently, Pap test collection in the Programme is available in 1790 gynaecological clinics across the country. Additionally, in 2011 family medicine practises employing certified midwives entered the Programme and 103 of them are currently actively collecting Pap smears. A modified Bethesda system (TBS) for evaluation and reporting of cytological results and a protocol derived from European Guidelines and Recommendations of the Polish Gynaecological Society is currently in practice [1–3]. In 2021, cytology was assessed in 74 laboratories around the country working within the OCCSP. Colposcopy in the Programme was performed in 62 clinics. The costs of medical procedures are reimbursed completely by the National Health Fund (NHF). The costs of quality assurance and coordination of the Programme are covered by the Ministry of Health. Data collected in the OCCSP are stored in the Electronic Screening Database called SIMP (pl.: System Informatyczny Monitorowania Profilaktyki). Quality assessments of the Programme are undertaken by the Central Coordination Centre based at the Maria Sklodowska-Curie National Research Institute of Oncology in Warsaw every year.

Recent data indicate a possible acceleration of the decreasing trend in the burden of cervical cancer (CC) after implementation of the OCCSP [4]. However, despite implementation of the Programme, there were still 2407 new cases (World Age Standardised Rate 7.3/100 000) and 1569 deaths due to CC (World Age Standardised Rate 3.9/100 000) in 2019 in Poland [5]. These rates are still higher than in Western European countries with well-established cancer prevention programmes. The factors explaining this unfavourable situation are low participation rate in the OCCSP – coverage of 14% reported in 2019, possible suboptimal performance of the Programme procedures including the screening test (conventional cytology) and triage and the very popular concurrent opportunistic screening of unknown coverage and quality [6]. Conventional cytology is the main primary screening test in the OCCSP. Liquid-based cytology (LBC) is available in a very small proportion.

Several countries have switched to screening with high risk Human Papillomavirus (hrHPV) testing because of its higher efficacy [7, 8]. The main advantage of HPV-based testing over cytological screening is its high sensitivity which reduces the risk for missing precancerous lesions and allows for extension of intervals between screening tests to five or more years [8]. According to the European Guidelines [2, 9], HPV-based screening programmes should be thoroughly evaluated in pilot studies before implementation. Since specificity of HPV testing is lower than that of cytology, more positive results are expected, with higher detection rates of high-grade lesions, but also of low-grade lesions requiring appropriate triage to avoid an increased burden of follow-up. European Guidelines recommend HPV testing alone and do not advocate HPV co-testing with cytology, because of the high costs, higher referral rate for an extremely small gain in protection [2, 8]. Triage of HPV positive women is still a subject of research and various algorithms are proposed [7]. HPV-based screening has been fully implemented in the Netherlands and women with positive test results are tested by reflex LBC twice in a 6-month interval in case of a first negative LBC sample [10]. A positive LBC result triggers colposcopic assessment.

Recently, new data appeared, e.g. on the use of immunohistochemical or molecular methods in triage of HPV positive women [7, 11]. The CINtec® PLUS Cytology test is a triage method for CC screening and simultaneously detects overexpression of p16 and Ki-67 which indicates transforming HPV infections [12]. The QIASURE methylation test is aimed at detecting hypermethylation of the promoters of the FAM19A4 and hsa-mir 124–2 genes [13]. Methylation of these genes indicates an ongoing carcinogenic process. Lack of methylation, in turn, indicates a low short-term risk of developing cancer. To our knowledge, performance of the two triage tests have not yet been compared prospectively in a screening programme.

## Aim

The HIPPO project (HPV testing In Polish POpulation-based cervical cancer screening program) was set up to evaluate and compare performance of an investigational screening strategy: i) HPV molecular testing with ii) current practice – conventional cytology/LBC in everyday clinical practice of the OCCSP in Poland. We also aim to compare performance of the CINtec® PLUS Cytology test and QIASURE methylation test as triage methods for HPV positive, twice LBC negative women in a screening programme.

## Methods

The project is designed as a randomised healthcare intervention nested in everyday practice of the OCCSP in Poland. It involves randomization of women attending screening into two arms according to the primary screening test applied: cytology (conventional or LBC, depending on the local site) and hrHPV test in a 1:1 ratio and age stratification into three strata: 30–39, 40–49 and 50–59 years. Since HPV testing in screening is not recommended for women younger than 30 years of age the project includes women aged 30–59 years [2]. The scheme of the project is presented in Fig. 1.

**Fig. 1 Fig1:**
[figure not shown]
The flowchart of women enrolled in the HIPPO trial. ASC-US—Atypical Squamous Cells of Undetermined Significance. CC – cervical cancer. hrHPV test—high risk Human Papillomavirus test. LBC—Liquid-Based Cytology. LSIL—Low-Grade Squamous Intraepithelial Lesion. NILM—No Intraepithelial Lesion or Malignancy

Inclusion criteria to the project are: i) age 30–59 and ii) without screening Pap test within the preceding three years (or one year for women with risk factors: HR HPV infection/HIV infection/use of immunosuppressive drugs entitled to annual screening based on information from the SIMP) in the OCCSP. Exclusion criteria for study are: the Pap test taken within the preceding three years in the OCCSP and illegibility for screening according to SIMP (previous treatment, hysterectomy etc.).

Women attending the selected screening sites are informed on the project by trained site personnel using pilot-tested information brochures with detailed information about the study, objectives of the study, duration, procedures, potential risks and benefits. By the decision of the Ministry of Health in Poland signing an informed consent is required from women to participate in the study. Women who accept participation are randomised by the SIMP to the competing screening tests and strategies. The sample takers and researchers involved in data collection and monitoring are aware of the arm to which each participant is assigned. The patients are informed about which arm they are also assigned to and they cannot change their arm. A questionnaire with screening history (participation in opportunistic screening, treatment of cervical lesions, HPV vaccination status etc.) are collected from participating women.

The primary endpoint is the detection rate (DR) of histologically confirmed CIN2 or higher in each screening arm and detection rate ratio (DRR) of CIN2 + in HPV test *vs* cytology arm in intention-to-treat (ITT) analysis. Secondary endpoints include detection rate ratio of CIN1 + , CIN3 + (including adenocarcinoma in situ) and invasive CC in both ITT and per-protocol (PP) analysis, restricted to women who adhered to the foreseen follow-up.

Other outcome measures are: (1) distribution of women by the screening test results; (2) referral rate for colposcopy; (3) compliance with referral for colposcopy; (4) positive predictive value of referral for colposcopy calculated for each screening test and separately by histology results (no CIN, CIN1, CIN2, CIN3, AIS, CIN2 + , CIN3 + , invasive cancer (squamous/adenocarcinoma)); (5) DR of histologically confirmed CIN2 + in patients with hrHPV positive test, two NILM LBCs six months apart and a positive CINtePlus Cytology and/or Qiasure test; (6) DRR of histologically confirmed CIN2 + after CINtec® PLUS Cytology test vs. QIASURE methylation test; (7) yield of use of CINtec® PLUS Cytology test vs. QIASURE methylation test in terms of detection rate of histologically confirmed CIN2 + .

Patients are recruited by the Cervical Cancer Prevention Clinic at the Department of Cancer Prevention at the Maria Sklodowska-Curie National Research Institute of Oncology in Warsaw (main centre) and 8 more sites from distant regions of Poland (Lublin, Masovian, Silesian, Swietokrzyskie and West Pomeranian Voivodeship). There are 24 gynaecological clinics, 9 diagnostic (cytological&molecular) laboratories and 10 colposcopy clinics. All sites are selected through a tendering process and have to fulfil several criteria for inclusion into the project (active participation in the OCCSP, being certified for HPV testing with the chosen clinically validated hrHPV DNA assays)to obtain results representative for the entire country.

The hrHPV tests are performed in diagnostic centres: Maria Sklodowska-Curie National Research Institute of Oncology ([name], [name] (branch in Gliwice)), Holy Cross Cancer Centre ([name]), Medical Center – Diagnostic ([name]), ALAB Laboratories ([name]), Non-public Health Care Center MEDITEST Medical Diagnostics ([name]), Non-public Health Care MULTIMED Gynecology and Obstetrics ([name]), Non-Public Health Care Department of Pathomorphology ALFAMED. [name], [name] ([name]), Femina. Medical Centre ([name]).

Site coordinators are contracted to monitor patients with abnormal screening test results in both arms. They are responsible for full acquisition and registration of histological outcomes. Coordinators regularly provide detailed reports to the main centre—Cancer Prevention Centre.

Additionally, biobanking of cytological samples taken from patients participating in the HIPPO project is performed in the Maria Sklodowska-Curie National Research Institute of Oncology for the purpose of potential future retrospective analyses if new CC screening or triage technologies emerge.

The study groups will be compared using two-sided tests: chi square test or analysis of variance (ANOVA, Kruskall-Wallis test). A chi-square test will be used to compare the characteristics of patients in different groups. The Kruskal–Wallis test will be used to compare differences in variables between two groups. If variations exist, a logistic regression analysis will be performed to permit control of potential confounding factors. The statistical significance in the experimental group compared with control will be analysed by ANOVA. Results will be considered statistically significant at the 0.05 significance level. The groups will be characterised by descriptive statistics: cardinality and percentage for discrete variables, mean and standard deviation for continuous variables with normal distribution, median and interquartile range for continuous variables with different distribution. The distribution of variables will be assessed among the groups. If variations exist, a logistic regression analysis will be performed to permit control of potential confounding factors. All analyses will be carried out with Stata 14.1 [14].

The study hypothesis assumes that the detection rate of histologically confirmed CIN2 + is significantly higher when HPV HR tests are used for screening in comparison to current standard of cytology (conventional or LBC).

There is scarce data on histological endpoints of the Polish OCCSP since the majority of colposcopy and biopsy procedures are performed outside the program and their results are not registered in the screening database. However, data on cytological results is fully available and credible. The data regarding the rate of high‐grade abnormalities (≥ ASC-H) results were extracted from the polish screening database. Some of them were conducted at OCCSP and had histopathological confirmation. Data extraction was used in analysis. Based on it, the rate of ASC-H or worse results is about 0.5% among screening Pap smears; therefore 0.5% is assumed as the baseline DR of CIN2 + in the control arm. Updated meta-analyses showed a relative sensitivity for CIN2 + of HPV test vs cytology of around 1.5 [8, 15–17]. As a consequence, the hypothesised DR of CIN2 + in the experimental HPV screening arm is 0.75%. Accepting the above assumptions, an alpha error of 5% and a power of 80%, each of the study arms should include around 16 500 women.

Based on SIMP, we calculated that the predicted referral rate for colposcopy is 1.3% and CC prevalence is 0.0134% in cytology arm.

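### Covariate adjustment is tied to observed baseline differences, with no fixed covariates, no stated status against the primary detection rate ratio, and no use of the randomisation age strata

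*Protocol article*

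**What the plan says.** All references are to the Protocol article.

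- **Design (Methods, opening paragraph).** Women are randomised "in a 1:1 ratio and age stratification into three strata: 30–39, 40–49 and 50–59 years".
- **Primary endpoint (Methods, endpoint paragraph).** This is the CIN2+ detection rate in each arm and the DRR of HPV testing against cytology, by ITT. Per-protocol analyses, restricted to women who adhered to follow-up, are listed with the secondary endpoints.
- **Analysis (Methods, statistical paragraph).** "The study groups will be compared using two-sided tests", at the 0.05 level. On baseline data: "A chi-square test will be used to compare the characteristics of patients in different groups". The same paragraph then says twice: "If variations exist, a logistic regression analysis will be performed to permit control of potential confounding factors". The second occurrence follows a sentence about assessing how variables are distributed among the groups, and no test is named there.
- **Not stated in that paragraph.** It does not say what counts as a variation, which covariates enter the model, or whether the model replaces or supports the DRR. It mentions neither age nor the strata.
- **Blinding (Methods).** Sample takers and the researchers who collect and monitor data know each woman's arm.

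**The concern.** Under correct randomisation, the ITT arms differ at baseline only by chance. Testing those differences says nothing about confounding, and a rule that starts from them decides whether to adjust on the basis of the data in hand. Age group, the one factor controlled in the design, is balanced by the stratification and so would rarely set the rule off. The rule therefore does not lead to an analysis that reflects how the women were randomised.

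The only adjusted model named is logistic. It returns an odds ratio, while the primary measure is a ratio of detection rates. With the model's status left open, two estimates of the main contrast may exist at the end and nothing written says which one governs. That is weak protection where data staff know the allocation, an interim analysis has already been presented (Timelines), and the results are to inform a national decision on the screening test (Discussion).

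**Working it through.** **1. Planning figure.** Inputs from the sample-size paragraph: "0.5% is assumed as the baseline DR of CIN2"+ in the control arm; the hypothesised rate "in the experimental HPV screening arm is 0.75"%; "an alpha error of 5% and a power of 80"%; two-sided; 1:1.

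Pooled formula: n = [1.960·√(2·p̄·q̄) + 0.842·√(p₁q₁ + p₂q₂)]² / (p₂ − p₁)², with p₁ = 0.005, p₂ = 0.0075, p̄ = 0.00625. This gives 15,599 per arm, or 16,389 with the continuity correction. The article's figure of about 16,500 is therefore reproduced. Power at 16,500 per arm is 82.2% without the correction. The point made here does not touch the sample size.

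**2. How often chance would trigger the model.** Assume that a variation means p<0.05 and that k independent characteristics are tested. Neither k nor the threshold is in the article. P(at least one) = 1 − 0.95^k.

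| k | 1 | 3 | 5 | 10 | 20 |
|---|---|---|---|---|---|
| Chance of trigger | 5% | 14% | 23% | 40% | 64% |

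**3. How small a difference would do it, on the same threshold.** For a characteristic with prevalence 50%: 1.96·√(2·0.25/16,500) = 1.08 percentage points. With prevalence 10%: 1.96·√(2·0.09/16,500) = 0.65 points.

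**4. Odds ratio against DRR.** DRR = 0.0075/0.005 = 1.500. Odds ratio = (0.0075/0.9925)/(0.005/0.995) = 1.504.

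**5. Effect on error rates.** Simulation with 16,500 per arm and 5,500 per age stratum. Assumptions: five independent binary covariates, each with prevalence 30% and an odds ratio of about 2 with outcome; relative CIN2+ risk by age stratum 1.0, 0.7 and 0.4. There were 3,000 trials with no effect and 2,000 with a ratio of 1.5. Under the conditional rule, only covariates with p<0.05 at baseline entered the model.

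| Analysis | Type I error | Power |
|---|---|---|
| Crude test | 5.2% | 81.5% |
| Conditional rule | 5.1% | 81.7% |
| Logistic model always adjusted for age stratum | 5.1% | 81.5% |

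The rule fired in 21% of trials. When it did, the log odds ratio moved by 0.009 on average and 0.027 at most. For scale, the planning rates imply 82.5 and 123.75 events, so the standard error of the log DRR is √(1/82.5 + 1/123.75 − 2/16,500) = 0.142. The largest shift seen is about a fifth of that (0.027/0.142 = 0.19).

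**The case against.** **The primary measure is already fixed.** A reader might infer that chance decides whether the headline result is a crude comparison or an adjusted odds ratio. The article does not support this. The endpoint paragraph names the ITT DRR as primary, and the analysis paragraph never says that an odds ratio takes its place. The logistic model can be read as supportive. What stands is that its status is not stated.

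**Age is not excluded.** A reader might also infer that the plan leaves age out of the model. The article names no covariates at all, and its wording about confounders could include age. A full protocol or analysis plan, not shown, may list it. Nor does the article say that every variable that differs will be entered. These are limits on the point. They do not rescue the trigger, which the article itself states, twice.

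**The trigger probabilities are conditional.** They need p<0.05 and an assumed number of independent tests. This is correct, and they are given only on that footing.

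**The numerical effect is close to nil.** This is also correct. Adjusting for a trivial imbalance changes the estimate trivially.

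**Adjustment has a legitimate use elsewhere.** The per-protocol analysis and the comparisons among referred women (predictive value, compliance) use groups formed after randomisation, where differences need not be chance. Striking out both sentences would remove that provision. This objection stands, so the change should be confined to the ITT comparison.

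**Conclusion.** The point holds as one about pre-specification and consistency with the design. The stated rule is unsound for randomised ITT arms, its covariates and threshold are open, its relation to the primary DRR is undefined, and the stated analysis does not use the age strata. It is not a claim of material bias or lost power: the two effect measures differ by 0.004 at the planning rates, and error rates were essentially unchanged in the one scenario simulated. That scenario rests on assumed covariates, and the 23% and 40% trigger figures rest on an assumed threshold and assumed independence. The change is worth making because it costs almost nothing and settles the primary estimate before the final data are seen.

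**What to change.** For the ITT comparison, replace the conditional wording with text to this effect:

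- The primary analysis is the CIN2+ DRR with its 95% CI, stratified by the three randomisation age groups (for example Mantel-Haenszel, or a modified Poisson model with log link and robust variance), regardless of baseline balance.
- Baseline characteristics of the ITT arms are reported descriptively. Tests on them do not trigger adjustment.
- Any further adjusted model is a sensitivity analysis, with covariates named in advance and the result on the ratio-of-rates scale.

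Keep adjustment for the per-protocol and referred-women comparisons, with those covariates also fixed in advance.

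Cost: a small change to the analysis wording. Age group is already recorded for randomisation, and the sample size is unaffected.

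### The test named for HPV versus cytology is ANOVA, which does not match a primary endpoint defined as a ratio of two rare detection rates

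*Protocol article*

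**What the plan says.** All of the relevant text is in the Methods section of the protocol article.

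- **Endpoints.** The primary endpoint is the detection rate of histologically confirmed CIN2+ in each arm, together with the "detection rate ratio (DRR) of CIN2 + in HPV test" versus cytology arm, by intention to treat. The secondary list continues in the same measure: "Secondary endpoints include detection rate ratio of CIN1 + , CIN3 + (including adenocarcinoma in situ) and invasive CC".
- **Tests, in general.** "The study groups will be compared using two-sided tests: chi square test or analysis of variance (ANOVA, Kruskall-Wallis test"). No endpoint is attached to this list.
- **Tests, by use.** Chi-square: "A chi-square test will be used to compare the characteristics of patients in different groups". Kruskal–Wallis: "The Kruskal–Wallis test will be used to compare differences in variables between two groups". ANOVA: "The statistical significance in the experimental group compared with control will be analysed by ANOVA". Logistic regression is conditional: "If variations exist, a logistic regression analysis will be performed to permit control of potential confounding factors".
- **Sample size.** The CIN2+ rates are taken as 0.5% (cytology) and 0.75% (HPV), with alpha 5% and power 80%, giving around 16,500 women per arm. For invasive cancer the text adds that "CC prevalence is 0.0134% in cytology arm".
- **Randomisation.** Allocation is 1:1, stratified by three age groups (30–39, 40–49, 50–59).

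**The concern.** Each woman either has CIN2+ detected or does not, and fewer than 1 in 100 are expected to. ANOVA is a method for comparing means. On 0/1 data it estimates a difference in proportions, while the primary endpoint is their ratio. The other named methods do not close the gap. Chi-square and Kruskal–Wallis produce a test statistic and a p-value. Logistic regression produces an odds ratio, and only if imbalances are found. No sentence says that the primary comparison will use the age strata on which women were randomised.

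At stake is the quantity the trial was set up to provide. The Discussion says the data will go to the Polish health technology agency for cost-effectiveness evaluation and a decision on switching the programme. That use needs the size of the gain in detection and its uncertainty. As the text stands, a crude ratio, an age-stratified ratio and an adjusted odds ratio could each be presented as the main result.

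**Working it through.** **Inputs (Methods).** p1 = 0.005, p2 = 0.0075, n = 16,500 per arm, alpha 0.05, power 0.80, invasive cancer prevalence 0.000134 in the cytology arm.

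**1. Which analysis was the trial sized for?** For two proportions, two-sided, with mean p̄ = 0.00625:

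n0 = [1.960·√(2·p̄(1−p̄)) + 0.8416·√(p1(1−p1) + p2(1−p2))]² / (p2−p1)² = 15,599 (rounded up).

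With the continuity correction, n = (n0/4)·[1 + √(1 + 4/(n0·0.0025))]² = 16,389. This reproduces the stated figure of around 16,500. The one-sided versions (12,287, or 13,075 corrected) do not. The trial was therefore sized as a comparison of two proportions.

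**2. What do the named methods return at the planned rates?** Expected cases are 16,500 × 0.005 = 82.5 and 16,500 × 0.0075 = 123.75. Take 82 and 124.

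| Method | p-value | Effect estimate |
|---|---|---|
| ANOVA on 0/1 data | 0.0033 (F = 8.62) | rate difference 0.25 percentage points (0.08 to 0.42) |
| Chi-square, uncorrected | 0.0033 (8.62) | none |
| Kruskal–Wallis | 0.0033 (8.62) | none |
| Logistic regression, unadjusted | – | OR 1.516 (1.146 to 2.006) |
| Ratio of rates (not named) | – | DRR 1.512 (1.145 to 1.997) |

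The DRR row is (124/16,500)/(82/16,500) = 1.512. The standard error of its logarithm is √(1/124 − 1/16,500 + 1/82 − 1/16,500) = 0.142, and the limits are 1.512·exp(±1.96 × 0.142).

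**3. Does using ANOVA distort the test?** No. In 400,000 simulated trials per setting, ANOVA and chi-square had the same type I error (5.0% at rates of 0.5% and 0.625%) and the same power (82.6% at the planned rates). A Wald test on the log DRR has 81.6% power at 16,500 per arm, so moving to the ratio needs no more women.

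**4. Invasive cancer.** Expected control-arm cases: 16,500 × 0.000134 = 2.2. If the ratio were 1.5 (an assumption borrowed from CIN2+), the HPV arm would expect 3.3. To show the precision, suppose 3 versus 2 cases. Conditional on 5 cases in equal arms, the exact 95% interval for the HPV share 3/5 is 0.147 to 0.947. As a ratio, share/(1 − share), that is 0.17 to 18.0 around an estimate of 1.5.

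**The case against.** **The primary inference is unharmed.** This stands. With two arms of 16,500 and a 0/1 outcome, the ANOVA F test is numerically the chi-square test. A reader who sees ANOVA applied to a rare event might infer a wrong error rate, lost power or a wrong sample size. The figures above support none of these.

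**Chi-square is also named for comparing the study groups.** This stands in part. It appears in the general list, so ANOVA is not the only option in the text. But the only specific use given to chi-square is patient characteristics, while the sentence on experimental versus control names ANOVA. Chi-square also yields no ratio.

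**The DRR will be reported anyway.** A crude DRR is the quotient of two reported rates, and at these rates the odds ratio is almost the same number. So it would be too strong to say that the trial will report no DRR. What no named method supplies is an interval for the ratio or an analysis that respects the strata.

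**An interval formula belongs in the SAP.** Its absence alone would not be a finding against a journal article. The point rests on what the article does state: a method for the main comparison that does not fit the endpoint. A SAP that did the sensible thing would depart from the published sentence.

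**Small cancer counts.** A reader might go further and infer that chi-square or ANOVA would wrongly declare significance for invasive cancer, since 5 versus 0 gives p = 0.025 against 0.062 by Fisher's test, and 7 versus 1 gives 0.034 against 0.070. That does not follow. Exact enumeration under equal rates with 2.21 expected cases per arm gives chi-square a type I error of 4.4% and Fisher 0.7%. Over 1.5 to 3.3 expected cases, chi-square stays at 3.0–4.7%. The gaps show that Fisher is conservative. The problem with cancer is imprecision.

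**Conclusion.** The point holds as a mismatch between the stated primary analysis and the primary estimand. The article defines the result as a DRR and sizes the trial on two proportions, then assigns the arm comparison to a method for means, with no stated use of the randomisation strata. Nothing elsewhere in the article corrects this.

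Its size is moderate. The CIN2+ p-value, type I error, power and sample size are unaffected. The cost lies in an effect estimate and interval that are not tied to the named analysis, and so in room to choose among close but different measures after the data are seen.

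This assumes one binary outcome per woman, about 16,500 women per arm and rates near those planned. The near-equality of odds ratio and DRR depends on the outcome staying rare. The SAP is not at hand and may already specify a ratio method. If so, the article's sentence still needs to be brought into line with it.

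**What to change.** Replace the ANOVA sentence with text such as:

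> The primary analysis is the intention-to-treat DRR of CIN2+ (HPV versus cytology) with a two-sided 95% confidence interval, stratified by the three randomisation age strata (e.g. Mantel–Haenszel risk ratio) and tested at the two-sided 5% level. CIN1+ and CIN3+ are analysed in the same way. ANOVA and Kruskal–Wallis are used only for continuous variables.

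Mantel–Haenszel is one suitable choice. A log-binomial or modified Poisson model with age stratum as a covariate would serve equally well. What matters is that one is named.

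For invasive cancer, report the counts by arm and an exact interval for the ratio, and say that the estimate will be very imprecise.

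The cost is a few sentences in the analysis section and the same wording in the SAP. No extra data are needed, and the sample size does not change.
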